## Abstract

**Background:**

The extensive use of neuromuscular blocking agents (NMBAs) during surgical procedures still leads to potential residual paralyzing effects in the postoperative period. Indeed, neuromuscular monitoring in an intra-operative setting is strongly advocated. Acetylcholinesterase inhibitors can reverse muscle block, but their short half-life may lead to residual curarization in the ward, especially when intermediate or long-acting NMBAs have been administered. Sugammadex is the first selective reversal drug for steroidal NMBAs; it has been shown to give full and rapid recovery of muscle strength, thus minimizing the occurrence of residual curarization. Acceleromyography of the adductor pollicis is the gold standard for detecting residual curarization, but it cannot be carried out on conscious patients. Ultrasonography of diaphragm thickness may reveal residual effects of NMBAs in conscious patients.

**Methods/design:**

This prospective, double-blind, single-center randomized controlled study will enroll patients (of American Society of Anesthesiologists physical status I–II, aged 18–80 years) who will be scheduled to undergo deep neuromuscular block with rocuronium for ear, nose, or throat surgery. The study’s primary objective will be to compare the effects of neostigmine and sugammadex on postoperative residual curarization using two different tools: diaphragm ultrasonography and acceleromyography of the adductor pollicis. Patients will be extubated when the train-of-four ratio is > 0.9. Diaphragm ultrasonography will be used to evaluate the thickening fraction, which is the difference between the end expiratory thickness and the end inspiratory thickness, normalized to the end expiratory thickness. Ultrasonography will be performed before the initiation of general anesthesia, before extubation, and 10 and 30 min after discharging patients from the operating room. The secondary objective will be to compare the incidence of postoperative complications due to residual neuromuscular block between patients who receive neostigmine and those who receive sugammadex.

**Discussion:**

Postoperative residual curarization is a topic of paramount importance, because its occurrence can cause complications and increase the length of stay in hospital and the related costs. Diaphragm ultrasound assessment may become a bedside integrative tool in the neuromuscular monitoring field to detect concealed residual curarization in surgical patients who have received paralyzing agents.

**Trial registration:**

EudraCT, 2013-004787-62. Registered on 18 June 2014, as “Evaluation of muscle function recovery after deep neuromuscular blockade by acceleromyography of the adductor pollicis or diaphragmatic echography: comparison between sugammadex and neostigmine.”

ClinicalTrials.gov,
NCT02698969. Registered on 15 February 2016, as “Recovery of Muscle Function After Deep Neuromuscular Block by Means of Diaphragm Ultrasonography and Adductor Pollicis Acceleromyography: Comparison of Neostigmine vs. Sugammadex as Reversal Drugs.”

**Electronic supplementary material:**

The online version of this article (10.1186/s13063-018-2525-7) contains supplementary material, which is available to authorized users.

## Background

Non-depolarizing neuromuscular blocking agents (NMBAs) are extensively used by anesthesiologists to maintain deep neuromuscular block (dNMB) during surgical operations. To avoid the postoperative residual effects of NMBAs, muscle relaxants should be fully catabolized to inactive metabolites prior to extubation. Nevertheless, when a patient is waking from general anesthesia, it is possible that some of the administered paralyzing agent is not completely transformed to its inactive form at the level of neuromuscular junctions, causing residual effects that can be difficult to clinically diagnose without adequate neuromuscular monitoring [1].

The use of intra-operative neuromuscular monitoring when NMBAs are administered has been encouraged in order to decrease postoperative residual curarization (PORC) [2]. Acceleromyography, the most commonly used method of quantitative monitoring, appraises muscle acceleration responding to nerve stimulation by train-of-four (TOF) and post-tetanic count (PTC) methods [3]. For many years, a TOF ratio not greater than 0.9 between the amplitude of the last stimulation and that of the first one was used to define PORC. Despite the fact that these types of monitoring are strongly recommended, they are not regularly performed in the operating room scenario [4, 5]. Furthermore, the TOF test is unpleasant for patients when they are conscious.

The incidence of PORC ranges from 9 to 56.5% when no reversal drug is administered [6]. For many years, reversing the NMBA effect has been carried out using an acetylcholinesterase inhibitor (AChEI) such as neostigmine. These inhibitors, which increase acetylcholine levels in the neuromuscular junction, antagonize the paralyzing agent but do not hasten its metabolism. Therefore, as a result of the unpredictable metabolism of blocking drugs, a residual curarization may occur when the AChEI effect has elapsed [7]. Indeed, an observational study showed that, 20 min after administration of neostigmine, 18% of patients had a TOF ratio < 0.9 [8]. Moreover, as shown in an animal study, when neostigmine is administered in the setting of full recovery from a muscle relaxant, the drug can cause weakness of the diaphragm and genioglossus muscle even if this effect is not seen when residual curarization is still present [9].

Sugammadex is the first selective reversal agent for steroidal NMBAs. It has been shown to give full and rapid recovery of muscle strength, thus minimizing the occurrence of PORC [8, 10].

The diaphragm, the major respiratory muscle in humans, is a great septum between the thoracic and abdominal cavities. The movement of the diaphragm accounts for 60–70% of the total tidal volume of respiration. Failure of diaphragmatic function is believed to play a central role in the pathophysiology of the clinical syndrome known as “pump respiratory failure” [11–13]. Although a TOF ratio > 0.9 in the adductor pollicis rules out residual curarization, the diaphragm is often not evaluated in the operating room. The diaphragm is the most highly resistant muscle to NMBAs, as well as the first to recover [14], but the occurrence of its dysfunction has been implicated in postoperative respiratory failure, especially when mechanical ventilation is prolonged [15, 16]. Therefore, studying diaphragmatic function in a perioperative context is extremely important.

Since 1985, ultrasonography has been used to evaluate diaphragm function by measuring thickness variations in the apposition zone, which reflect the extent of contraction of the muscle [17]. Vivier et al. recently demonstrated that the thickening fraction (TF), namely the difference between the thickness at the end of inspiration (TEI) and that at the end of expiration (TEE), normalized for TEE (TEI – TEE/TEE), is directly related to respiratory workload, and they suggested that TF could be used as an index to select those patients ready to be weaned from non-invasive ventilation [18]. These data suggest that ultrasound TF could also be used in different scenarios, and our purpose is to use ultrasound TF to assess diaphragm recovery after dNMB since it is more comfortable for conscious patients than acceleromyography.

We therefore hypothesize that the incidence of postoperative diaphragmatic dysfunction, assessed using ultrasonography and, from our unpublished observations, defined by a fractional shortening of the diaphragm < 40%, is lower in patients who receive sugammadex than in those who receive neostigmine.

## Methods/design

### Study design and eligibility

This study is a prospective, double-blind, randomized controlled trial involving 60 patients with American Society of Anesthesiologists (ASA) physical status I–II and aged between 18 and 80 years, who will undergo dNMB (standard care in our clinic) with rocuronium during ear, nose, or throat surgery in a university hospital. The Institutional Review Board of the Tuscany Region has approved the protocol with registration number CE SPE 13.068. Exclusion criteria are a history of hepatic or renal disease, chronic or acute alcoholism, allergy or hypersensitivity to sugammadex or neostigmine, current medication with effects on the central nervous system, a history of neurologic disease, diaphragmatic palsy, women who are pregnant or nursing, and arrhythmias.

### Randomization

Written informed consent will be obtained during the preoperative evaluation by an anesthesiologist working in the anesthesia unit of the hospital. Afterwards, each patient will be randomly allocated to either the sugammadex (SUG) group or the neostigmine (NEO) group. Randomization will be performed using a table created on www.randomization.com. The allocation plan will be carried out using a variable block randomization method 1:1 to distribute the patients equally to each group. For allocation concealment, table assignment to one group or the other will be managed by a pharmacist with limited involvement in the study; this person will also perform the allocation and prepare the drugs.

### Intervention plan

In order to standardize the anesthetic technique, no premedication will be administered. All patients will undergo neuromuscular monitoring with ulnar nerve stimulation using the TOF-Watch (Organon, Oss, Netherlands). The device will be calibrated preoperatively, and the parameters will be set using standard TOF methodology after administration of a hypnotic drug, prior to muscle relaxation. General anesthesia will be induced by intravenous injection of fentanyl (2 μg/kg body weight), propofol (2 mg/kg), and rocuronium (0.6 mg/kg). Tracheal intubation will be performed after the patient fails to register signals using TOF. To maintain dNMB, rocuronium (0.15 mg/kg) will be re-administered when the PTC elicits more than five twitches. Sevoflurane will be supplied at an age-adjusted end-tidal concentration of 1.0 minimum alveolar concentration (MAC) in an air/oxygen mixture. Fentanyl will be titrated with a bolus of 0.5 μg/kg every 30 min, to keep an adequate level of analgesia.

Prior to induction of anesthesia, the baseline TF will be evaluated by one operator skilled in ultrasonography using an Esaote MyLab ultrasound instrument (Esaote, Genoa, Italy). Patients will be placed on the bed in a semi-recumbent (45°) position, assessed by a goniometer. The operator will use a 10–12 MHz high-frequency linear probe to identify the diaphragm in the midaxillary line in the apposition zone between the lung and liver on the right and between the lung and spleen on the left, in the intercostal spaces between the ninth, tenth, and eleventh ribs, 0.5–2 cm above the costophrenic sinus. The TF will be calculated at tidal breathing, recorded in time-motion mode. The muscle will be located using the hyperechoic pleural and peritoneal layers. Three assessments will be performed in consecutive breaths and averaged [18].

At the end of the operation and when TOF neuromuscular monitoring shows a minimum of two twitches, patients will receive the reversal drug according to the group to which they have been randomized. Patients in the NEO group will receive 50 μg/kg neostigmine and 15 μg/kg atropine, while those in the SUG group will receive 2 mg/kg sugammadex [19]. The drugs will be prepared for intravenous injection in identical volumes and in indistinguishable syringes so that the anesthesiologist will be blinded to the treatments the patients receive. Extubation will be performed when all the following criteria are met: (1) the patient is awake and can execute simple commands; (2) the patient’s respiratory pattern is regular with a tidal volume of 6–7 mL/kg referred to ideal body weight; (3) the TOF ratio is > 0.9. Immediately prior to extubation, bilateral diaphragm ultrasonography will be performed to assess muscle recovery in spontaneously breathing patients; these measurements will be compared to the baseline muscle assessment. Two additional diaphragm ultrasound scans will be performed 10 and 30 min after discharge from the operating theater under the same conditions as described above, but no further TOF monitoring will be carried out. Follow-up will be performed to document adverse events and complications until discharge from the hospital. The physician who performs the ultrasound scan will be different from the one who administers the reversal drug and will be blinded to the treatment that patients receive (Figs. 1 and 2). The Standard Protocol Items: Recommendations for Interventional Trials (SPIRIT) checklist is provided as Additional file 1.

**Fig. 1 Fig1:**
[figure not shown]
Study timeline

**Fig. 2 Fig2:**
[figure not shown]
Study flow diagram

In the case of unexpected events, such as a change in drug dose or a participant’s request to withdraw from the study, the protocol will be stopped and this will be recorded on the case report form (CRF). No further tests will be performed except those necessary to finalize the protocol. Should patients need medical care that interferes with the correct conduct of the study, they will be excluded from the study.

The primary endpoint of the study will be a 30% relative reduction in the incidence of residual curarization in patients who receive sugammadex compared with neostigmine 30 min after drug administration. The primary endpoint will be assessed at 30 min because the effects of neostigmine start to fade after this time has elapsed [20]. Residual curarization will be determined by the percentage of 30 min TF compared to baseline TF. It is not known exactly what percentage TF indicates residual curarization, but from our unpublished observations, values of 40% or less could indicate diaphragmatic dysfunction. However, we do not know what percentage of patients have a TF < 40% when neostigmine is administered.

Two secondary endpoints will be assessed. One secondary endpoint will be a 10% relative reduction in respiratory complications related to residual curarization obtained with sugammadex compared with neostigmine. Respiratory complications taken into consideration will be new cough and sputum production, abnormal breath sounds not present at baseline, temperature higher than 38 °C, chest radiography documentation of atelectasis or new infiltrates, and physician documentation of atelectasis or pneumonia [21]. The other secondary endpoint will be a 30% relative decrease in postoperative nausea or vomiting in patients who receive sugammadex compared with those who receive neostigmine.

Data monitoring will be performed by an anesthetist not involved in the study. Data will be collected on paper CRFs. All personal information will be registered in an environment limited to medical personnel to maintain absolute confidentiality. Data entry will be performed at one central site that maintains the overall database and will carry out the data analysis. All the compiled CRFs will be archived in a locker to which only clinicians involved in the study have access. In order to eliminate possible data entry errors, individual data will be compared to a range of plausible values. After data entry, automated checks, which have been defined a priori, will be performed to search for internal inconsistencies, range errors, or missing data. For each atypical, out-of-range, or missing datum, a query will be automatically sent to the investigator. Once all the queries are solved, the database will be locked and used for statistical analysis. All the individual participant data collected during the trial, after de-identification, will be available. The study protocol, statistical analysis plan, and analytic code will be accessed beginning 3 months and ending 5 years following article publication by researchers who will provide a methodologically sound proposal to achieve aims in the approved proposal. Each request must be sent to the corresponding author.

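### Randomised patients who need interfering care are excluded, and others are stopped, with no exception for care prompted by weakness, so loss from the comparison can depend on treatment and outcome

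*Protocol article*

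**What the plan says.** Allocation follows consent at the preoperative evaluation (Randomization): "Afterwards, each patient will be randomly allocated to either the sugammadex (SUG) group or the neostigmine (NEO) group". Anything that happens at or after reversal is therefore post-randomisation.

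The text after Fig. 2 in the Intervention plan contains two separate rules.

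- **Stopping.** "In the case of unexpected events, such as a change in drug dose or a participant’s request to withdraw from the study", the protocol is stopped and this is recorded on the case report form. Then: "No further tests will be performed except those necessary to finalize the protocol". The tests covered by that exception are not named.
- **Exclusion.** "Should patients need medical care that interferes with the correct conduct of the study, they will be excluded from the study". Interfering care is not defined.

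The primary outcome depends on the late scan: "Residual curarization will be determined by the percentage of 30 min TF compared to baseline TF". For complications, the Intervention plan says: "Follow-up will be performed to document adverse events and complications until discharge from the hospital". It does not say whether this continues for stopped or excluded patients.

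The section on statistical analyses and sample size models ΔTF by generalized estimating equations and linear regression, adjusted for time and baseline TF. For excluded patients it mentions descriptive statistics only.

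**The concern.** Both rules act after allocation, and what triggers them can be affected by the allocated drug. A patient who recovers slowly or weakens again is a plausible candidate for more reversal drug (a dose change) or for respiratory support (interfering care). The first can cost the 30-min scan. The second leads to exclusion. Neither rule separates this kind of care from care unrelated to muscle function.

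The trial's hypothesis is that dysfunction is more frequent after neostigmine. If it is true, such losses would be unequal between arms and concentrated among patients with the outcome. Blinding does not prevent this, because the trigger is the patient's state. What is at stake is whether the two groups analysed are still the two groups randomised. For the secondary respiratory endpoint, it is also whether a complication that needs treatment could take the patient out of the count.

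**Working it through.** **1. Order of events.** Consent, then 1:1 allocation (Randomization), surgery, reversal, scan before extubation, and scans 10 and 30 min after leaving the theatre (Intervention plan). Both rules can act between reversal and the last scan.

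**2. What each rule removes.**

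| Trigger | Stated consequence | Effect on the 30-min outcome |
|---|---|---|
| Unexpected event, e.g. dose change or withdrawal request | Protocol stopped; no more tests, with an undefined exception | Scan ordinarily lost, unless the exception covers it |
| Interfering medical care | Excluded from the study | Patient leaves the comparison |

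**3. Room for loss.** The sample size section allows 5% for TF that cannot be evaluated: 0.05 × 30 = 1.5 patients per arm. It states no allowance for exclusions.

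**4. Expected events.** Inputs from the sample size section: 30 per group, 23–25% with neostigmine, 2–4% with sugammadex. A two-sided pooled comparison of 24% with 3% at 80% power needs 41 per group, or 41/0.95 = 43.2, rounded up to 44, with the 5% allowance. The stated 30 is therefore not reproduced at the midpoints. That is a separate matter, and 30 is used here as given.

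- Neostigmine: 0.24 × 30 = 7.2 (range 6.9 to 7.5)
- Sugammadex: 0.03 × 30 = 0.9 (range 0.6 to 1.2)
- Difference: 24 − 3 = 21 points

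**5. Illustration A: k neostigmine events lost, none with sugammadex.** Rate = (7.2 − k)/(30 − k). The values of k are an assumption.

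| k | Neostigmine rate | Difference from 3% |
|---|---|---|
| 0 | 7.2/30 = 24.0% | 21.0 points |
| 1 | 6.2/29 = 21.4% | 18.4 points |
| 2 | 5.2/28 = 18.6% | 15.6 points |
| 3 | 4.2/27 = 15.6% | 12.6 points |

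**6. Illustration B: the same fraction f of events lost in both arms.** Rate = p(1 − f)/(1 − pf).

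| f | Neostigmine | Sugammadex | Difference |
|---|---|---|---|
| 10% | 22.1% | 2.7% | 19.4 points |
| 25% | 19.1% | 2.3% | 16.9 points |
| 50% | 13.6% | 1.5% | 12.1 points |

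The difference shrinks even when the rule acts on events equally in both arms, because neostigmine has more events to lose.

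**7. Direction is not guaranteed.** If two neostigmine patients without the outcome were lost instead, the rate would be 7.2/28 = 25.7% and the difference 22.7 points. The sign of the bias depends on who is removed.

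No power figures are attached. The named primary model is for ΔTF, and power for a comparison of two proportions would not describe it.

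**The case against.** The strongest reply has five parts.

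- **The rules are narrower than they look.** A reader might infer that a dose change leads to exclusion. The text does not say so: it leads to stopping, and the exception for tests needed to finalize the protocol could be read to include the 30-min scan. This stands. What remains is that the exception is undefined.
- **The link to the outcome is an inference.** A reader might conclude that the rules remove the very patients who have residual curarization. The documents do not establish this. Extubation waits for recovery criteria that include a TOF ratio above 0.9, so slow recovery may only delay it. The Discussion part of the Abstract speaks of concealed residual curarization, which need not prompt any care. This stands as a limit on certainty and size; the missing exception for weakness-related care remains.
- **Most listed respiratory complications would appear after the last scan**, when treatment has little left to interfere with. General follow-up and a specific exclusion can also be read as rule and exception. This largely stands: the two passages sit uneasily together but do not flatly contradict each other.
- **The planned model uses repeated scans**, so a patient without the 30-min scan may still contribute earlier ones. That is true for stopped patients, and it helps excluded patients only if their data are kept.
- **Analysis sets commonly sit in the statistical analysis plan**, which the article mentions and which is not shown. This would answer a complaint about silence. Here the article states an exclusion, which an analysis plan would have to override.

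**Conclusion.** The point holds as a defect in a stated rule. Followed as written, it takes randomised patients out of the study for reasons that can depend on treatment and outcome, and it leaves unclear whether stopped patients keep their 30-min scan. The likely direction is toward no difference if losses fall mainly on affected neostigmine patients. Even then the rule would not manufacture a benefit for sugammadex.

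The size is unknown, because the article gives no expected number of stopped or excluded patients. The fall from 21 to about 18, 16 or 13 points rests on two assumptions: the planned midpoint rates are right, and one, two or three neostigmine events and no sugammadex events are lost. It shows only that with about 7 and 1 expected events a few patients matter. It should not be read as an estimate of bias in this trial or as a loss of power in the ΔTF model.

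**What to change.** According to Trial status, recruitment is complete, all data are collected and analysis has not begun. The change is therefore to the analysis, to be made before unblinding:

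1. Replace the exclusion with analysis of all randomised patients in their allocated arm.
2. Use every available scan in the ΔTF model and all complication data recorded to discharge, unless consent to use the data is withdrawn.
3. Report stopped and excluded patients by arm and reason, including which scans each one has.
4. Present the analysis without these patients only as a sensitivity analysis.
5. For the binary residual-curarization endpoint, add a sensitivity analysis that counts as events those patients who had additional reversal or airway or ventilatory support for weakness before the 30-min scan. This cannot supply a missing ΔTF and is written after data collection, so it should not be the primary definition.

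The cost is retrieval of some case report forms, where stops are already recorded, and a few missing scans to handle. No treatment or clinical procedure changes.

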### Statistical analyses and sample size calculation

The statistical analysis will be performed by an independent statistician using SAS 9.3 (SAS Institute, Inc., Cary, NC, USA). For the primary endpoint, the effect of a drug on ΔTF will be estimated using generalized estimating equations (GEEs) and a multiple linear regression model adjusting for time of the measurement and baseline TF of the right side. This hemidiaphragm has been chosen because it is more easily identified for the presence of the liver. For the secondary endpoint, the association between a drug and its collateral effect will be evaluated using a logistic regression model. *P* values lower than 0.05 have been considered statistically significant.

Finally, descriptive statistics of all variables describing the characteristics of the patients enrolled in the study and those excluded from the study will be analyzed. Continuous variables will be expressed as mean (± standard deviation, (SD)) and median (ranging from 25th to 75th percentiles). Percentages will be calculated for dichotomous data. For categorical variables, frequency counts and percentages will be calculated.

Since this is the first clinical trial that proposes, as its primary endpoint, a relative reduction of 30% in the incidence of residual curarization, the necessary sample size has been calculated using the statistical software Epi Info (version 7). This analysis shows that at least 30 patients per group will be necessary, considering that in 5% of subjects TF is not valuable [22, 23], and expecting 23–25% of residual curarization with neostigmine 30 min after the extubation vs. 2–4% after the administration of sugammadex (with a 95% confidence interval (CI) and a power of 80%, and assuming equal variance between the two groups). For the secondary outcome, the number needed to treat has been calculated with a CI of 95%.

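### The declared target is a 30% relative reduction, but the trial was sized on an 83–92% reduction; an incidence comparison with 30 per group has about 10% power for the declared target

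*Protocol article*

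**What the plan says.** In Methods/design, the endpoint paragraph after Figure 2 states: "The primary endpoint of the study will be a 30% relative reduction in the incidence of residual curarization". It compares sugammadex with neostigmine at 30 minutes and adds that the share of neostigmine patients below the 40% threshold is not known.

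The section Statistical analyses and sample size calculation describes the trial as the first to propose "as its primary endpoint, a relative reduction of 30% in the incidence of residual curarization", and that sentence introduces the calculation. It concludes that "at least 30 patients per group will be necessary", after allowing for 5% of patients without an evaluable TF, and "expecting 23–25% of residual curarization with neostigmine 30 min after the extubation vs. 2–4% after the administration of sugammadex". The terms are 95% confidence and 80% power, and for the analysis P "values lower than 0.05 have been considered statistically significant". The design section gives the same size: "randomized controlled trial involving 60 patients".

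The same statistical section assigns the primary endpoint to generalized estimating equations and a linear regression on ΔTF, a continuous variable, adjusted for time and baseline TF.

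**The concern.** The effect declared as the target and the effect used to set the sample size differ greatly, and the article presents the first as the reason for the second. A reader would take 60 patients to be enough for a 30% relative reduction. If the incidence comparison then came out non-significant, it could be read as evidence against a 30% reduction that the trial had little chance of detecting. The endpoint is also written as a between-group result rather than as something observed in each patient, so the text does not say what is counted.

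**Working it through.** **Inputs from the article.** Neostigmine rate p1 = 23–25%; planned sugammadex rate 2–4%; declared relative reduction 30%; 30 per group, 1:1; 80% power; 5% not evaluable. Significance level 0.05, read as two-sided because sidedness is not stated.

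**1. Effect implied by the planning rates.**
- Smallest relative reduction: 1 − 4/23 = 0.826. Largest: 1 − 2/25 = 0.920.
- Absolute difference: 23 − 4 = 19 points to 25 − 2 = 23 points.
- Neither the relative nor the absolute reading gives 30%.

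**2. The article's own sample size.** Pooled two-proportion formula, with p̄ = (p1 + p2)/2:

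n = [1.96·√(2p̄(1−p̄)) + 0.842·√(p1(1−p1) + p2(1−p2))]² / (p1 − p2)²

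| Rates | n per group | after dividing by 0.95 |
|---|---|---|
| 25% vs 2% | 34 | 36 |
| 24% vs 3% | 41 | 44 |
| 23% vs 4% | 50 | 53 |

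The stated 30 is not reproduced on two-sided terms. A one-sided 0.05 test at 24% vs 2% gives 28, then 30 after the allowance, but the article does not state a one-sided test.

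Power with 30 per group, before any loss:

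| Rates | Normal approximation | Exact, uncorrected chi-square | Exact, Fisher |
|---|---|---|---|
| 25% vs 2% | 75% | 84% | 63% |
| 24% vs 3% | 67% | 75% | 52% |
| 23% vs 4% | 58% | 64% | 41% |

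**3. The declared 30% reduction.** Here p2 = 0.70·p1. Power = Φ{[(p1 − p2) − 1.96·√(2p̄(1−p̄)/30)] / √([p1(1−p1) + p2(1−p2)]/30)}.

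For 24% vs 16.8%: difference 0.072; critical difference 0.204; standard error 0.1036. Then (0.072 − 0.204)/0.1036 = −1.27, and Φ(−1.27) = 0.10.

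| Rates | Power, n = 30 | Exact chi-square | Fisher | n per group for 80% |
|---|---|---|---|---|
| 23% vs 16.1% | 9.8% | 10.0% | 5.3% | 518 |
| 24% vs 16.8% | 10.1% | 10.3% | 5.7% | 491 |
| 25% vs 17.5% | 10.5% | 10.6% | 6.0% | 466 |

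**4. Sensitivity.** A one-sided test gives 16–17%. With 28 evaluable per group the two-sided figure is 9.4–10.0%. The article says the control rate is unknown; if it were 40%, power for a 30% reduction would be about 16%.

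**5. What a null result would show.** At 24% vs 16.8% the 95% CI half-width is about 1.96 × 0.1036 = 0.203. An observed difference equal to the declared target would be 7 points with an interval of about ±20 points, which includes both no difference and differences much larger than the target.

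**The case against.** **The planned analysis is not a comparison of proportions.** This stands. The primary model is for continuous ΔTF with repeated measurements. A reader might infer that the whole trial has 10% power, but the article does not support that: it gives no SD or mean difference, so the power of the ΔTF model cannot be computed. The 10% belongs to the incidence endpoint. That endpoint is nevertheless the one declared, and incidence is what the sample size was computed from.

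**Thirty percent may be a minimum relevant effect, with a larger effect expected.** Two such figures can coexist, so they are not contradictory in principle. The article does not make this distinction, though, and ties the 30% to the calculation in the sentence "a relative reduction of 30% in the incidence of residual curarization, the necessary sample size has been calculated". Even on this reading, power at the minimum effect should be disclosed.

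**Two stronger readings go too far.**
- A reader might conclude that only near-abolition of events could reach significance. That holds only near the assumed rate: by uncorrected chi-square, 7 vs 1 events gives p = 0.023 and 7 vs 2 gives p = 0.071. At higher control rates smaller reductions suffice: 12 vs 5 gives p = 0.045 and 15 vs 7 gives p = 0.032. The control rate is stated to be unknown.
- A reader might suppose that any observed reduction of at least 30% counts as success. The article states no such rule; its criterion is P below 0.05.

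**Recruitment is complete.** The sample size cannot change, but the article says analysis has not begun, so the wording can still be corrected.

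**Conclusion.** The point holds for the incidence endpoint. The declared target (30% relative) and the sizing assumption (83–92% relative) are not reconciled anywhere in the article. Power for the declared target is about 10% with 30 per group, assuming a two-sided 0.05 comparison of two proportions and a neostigmine rate of 23–25%. It stays low under the alternatives tried. A non-significant incidence result could not rule out a 30% reduction. Nothing here measures the power of the ΔTF model. Separately, 30 per group falls short of 80% over most of the article's own planning range, and over all of it by Fisher's test or the normal approximation.

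**What to change.** Issue a dated, documented clarification before the analysis starts. Because the data are already collected, the 30% should not simply be deleted. The clarification should:

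1. Define the primary endpoint as a patient-level event, present or absent at the 30-minute scan. Reconcile the time origin, which is leaving the operating theatre in the intervention plan, drug administration in the endpoint paragraph, and extubation in the sample-size paragraph.
2. State that 23–25% against 2–4% was the planning assumption. State also that 30 per group gives roughly 64–84% power for it by uncorrected chi-square (41–63% by Fisher), before the 5% non-evaluable loss.
3. Withdraw 30% as the powered target, or state that power for it is about 10% in an incidence comparison.
4. Add a binary analysis that matches the endpoint, reporting the risk difference with its 95% CI alongside the ΔTF model.

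The cost is wording and one additional analysis; sample size and conduct do not change. The downside is that the stated detectable effect and power become less favourable than the article now suggests.
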